## Abstract

**Background::**

Total knee arthroplasty (TKA) is known to be a painful orthopedic procedure and moderate to severe pain is common, especially immediately postoperatively and during active motion. The aim of the present study was to compare epidural analgesia (EA) and adductor canal block (ACB) techniques with regard to early period pain levels, need for additional opioids, and ambulation and functional scores in patients who had undergone primary TKA.

**Methods::**

Approval for the study was granted by the Changji Branch of the First Affiliated Hospital of Xinjiang Medical University. Written informed consent will be obtained from all of the participants. Inclusion criteria included the following: planned unilateral TKA; spinal anesthesia; American Society of Anesthesiologists physical status classification score of I to III. Prospective assessment will be done for 100 patients who are scheduled for unilateral primary TKA surgery in our academic hospital by a single senior surgeon between August 2020 and December 2021. Patients were randomized to ACB treatment or EA treatment by a computer random number generator. The primary outcome was visual analog scale pain scores in the immediate postoperative period. Secondary outcomes included postoperative opioid use, length of hospital stay, activity level during physical therapy, and knee range of motion. Results were evaluated in a confidence interval of 95% and at a significance level of *P* < .05.

**Conclusions::**

We hypothesized that standard ACB would be as effective as EA for postoperative pain management following TKA.

**Trial registration::**

This study protocol was registered in Research Registry (researchregistry5775).

## Introduction

1

The prevalence of knee osteoarthritis is increasing world-wide due to the aging population. A standard surgical intervention for advanced knee osteoarthritis is total knee arthroplasty (TKA), and demand for this surgery is rising.^[1]^ TKA is known to be a painful orthopedic procedure and moderate to severe pain is common, especially immediately postoperatively and during active motion.^[2,3]^ The proportion of patients complaining of chronic pain after TKA is as much as 34%, and the intensity of early postoperative pain is associated with increased chronic pain after TKA. Therefore, postoperative pain management is of utmost importance for patient outcome and satisfaction, and many studies have reported that multimodal pain management was necessary.^[4,5]^

Patient-controlled analgesia, local infiltration analgesia, epidural analgesia (EA), femoral nerve block (FNB), and adductor canal block (ACB) are some methods that may manage the postoperative pain and shorten the physiotherapy duration, but the most efficacious remains unclear.^[6,7]^ EA consisting of a local anesthetic agent and an opioid has been a regular regimen used for postoperative analgesia after TKA. However, some studies have indicated that the benefit of EA must be weighed against the frequency of its adverse effects such as urinary retention, hypotension, pruritus, and motor block that delays mobilization.^[4,8–10]^ FNB has traditionally been the gold standard for analgesia following TKA, but FNB significantly impairs quadriceps motor function, which may interfere with rehabilitation and delay discharge. ACB has emerged as an alternative to FNB after TKA. ACB offers the advantage of sparing the motor nerve supply to most of the quadriceps muscle, which may facilitate physiotherapy after TKA and may lead to a reduction in falls after surgery. ACB is commonly integrated into a multimodal pain protocol to improve pain management after TKA.^[11–14]^

However, while studies exist comparing FNB to EA and FNB to ACB,^[8,9,15]^ there have been limited studies directly comparing ACB to EA in terms of postoperative pain control and ambulation after primary TKA.^[16–18]^ Thus, the aim of the present study was to compare EA and ACB techniques with regard to early period pain levels, need for additional opioids, and ambulation and functional scores in patients who had undergone primary TKA. We hypothesized that standard ACB would be as effective as EA for postoperative pain management following TKA.

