### Study design and patient enrolment

2.1

Approval for the study was granted by the Changji Branch of the First Affiliated Hospital of Xinjiang Medical University (CJ97440). Written informed consent will be obtained from all of the participants. Prospective assessment will be done for 100 patients who are scheduled for unilateral primary TKA surgery in our academic hospital by a single senior surgeon between August 2020 and December 2021. Our study was registered in Research Registry (researchregistry5775) prior to the enrollment start. All surgeons, recovery room and floor nurses, research assistants, statisticians, and patients were blinded to group allocation. Only the anesthesiologists performing the blocks and operating room nurses were not blinded.

Inclusion criteria included the following: planned unilateral TKA; spinal anesthesia; American Society of Anesthesiologists physical status classification score of I to III. Exclusion criteria included the following: unwillingness to participate in the study; general anesthesia; contraindications for the application of ACB such as localized infection and neurological disease in the lower extremity; history of epilepsy; arrhythmia; alcohol or drug dependency; known allergy to local anesthetics; insufficient co-operation for the completion of the visual analog scale (VAS) for pain scores; patients who had an inability to communicate verbally or who were unwilling to give informed consent; American Society of Anesthesiologists physical status classification score of IV.

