### Sample size calculation

2.6

The sample size calculation was based on a pilot study that we conducted on 20 patients. In this prior study, the mean difference and standard deviation of the VAS scores on postoperative day 0 between the ACB and EA groups were 0.42 and 0.21, respectively. From this, it was determined that 50 subjects would be required to reach an α value of 0.05 and a power of 90%. It was estimated that the attrition rate due to canceled surgery or reasons of late patient ineligibility could be up to 20% and, therefore, to account for this, the final sample size selected was n = 120 (60 per group).

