### Statistical analysis

2.7

Statistical analyses were conducted using SPSS v22.0 software (IBM, Chicago, IL). Conformity of the data to normal distribution was tested with the Kolmogorove–Smirnov test. Independent two samples *t* test was used for comparison of continuous variables and Pearson Chi Square test was used for comparison of categorical variables. Results were evaluated in a confidence interval of 95% and at a significance level of *P* < .05.

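### The hypothesis claims comparable efficacy of ACB and EA, but the trial is sized and tested for a difference, with no margin, so a non-significant result could not support it

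*Protocol article*

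**What the plan says.** The Introduction ends with a neutral aim, to compare the two techniques, followed directly by the hypothesis: "We hypothesized that standard ACB would be as effective as EA for postoperative pain management following TKA". The same hypothesis is the only content of the abstract's Conclusions and returns in the Discussion. No other hypothesis is stated.

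Two sections bear on how it will be tested:

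- **Sample size calculation (2.6).** "The sample size calculation was based on a pilot study that we conducted on 20 patients". The mean difference and standard deviation of the "VAS scores on postoperative day 0 between the ACB and EA groups were 0.42 and 0.21", and from these "it was determined that 50 subjects would be required to reach an α value of 0.05 and a power of 90" percent. After an allowance for attrition, "the final sample size selected was n = 120 (60 per group").
- **Statistical analysis (2.7).** "Independent two samples *t* test was used for comparison of continuous variables". Results are to be judged with a 95% confidence interval and at P < .05.

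Neither section, nor any other, gives a non-inferiority or equivalence margin, a rule for setting the confidence interval against one, the sidedness of the test, or the meaning to be given to a non-significant result.

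**The concern.** A claim that one technique works as well as another needs evidence that any deficit is smaller than some amount judged acceptable. The null hypothesis is then a deficit at least as large as that amount. The t test in section 2.7 has the other null, no difference, and section 2.6 sizes the trial to reject that null. Failing to reject it shows only that the data did not separate the groups, which also happens when the data are noisy or few.

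At stake is the trial's main conclusion. If ACB is somewhat worse than EA, the plan may return P >= .05, and nothing in the article guards against reporting that as confirmation of the hypothesis.

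**Working it through.** **Inputs.** From section 2.6: difference 0.42, SD 0.21, alpha 0.05, power 90%, 50 subjects before attrition. I read the 50 as per group, because the final size is 60 per group (50 x 1.2 = 60). Section 2.1 ("Prospective assessment will be done for 100 patients") also gives 50 per group if allocation is equal. From section 2.7: independent t test, P < .05. Assumptions: two-sided test, since sidedness is not stated; higher VAS means more pain.

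**1. The plan's own figure.** For two means, n per group = 2 x [(1.960 + 1.282) x SD / difference]^2 = 2 x (3.242 x 0.21 / 0.42)^2 = 2 x 1.621^2 = 5.3, so 6 per group (7 with the t distribution). The stated 50 is not reproduced. It would correspond to SD = 0.42 / (3.242 x sqrt(2/50)) = 0.65. That discrepancy is a separate matter. It is relevant here because it leaves the SD uncertain, so the results below are in SD units. The form of the calculation, a between-group difference with alpha and power, is sizing for a difference.

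**2. How often the planned test is non-significant when ACB is truly worse.** With n per group and true deficit d in SD units, the t statistic is noncentral t with 2n - 2 degrees of freedom and noncentrality d x sqrt(n/2). At n = 50, sqrt(25) = 5 and the critical value is 1.984.

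| True deficit (SD) | Noncentrality | P(non-significant) |
|---|---|---|
| 0.3 | 1.5 | 68% |
| 0.4 | 2.0 | 49% |
| 0.5 | 2.5 | 30% |
| 0.648 | 3.24 | 11% |

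With all 60 per group retained, the first three become 63%, 42% and 22%.

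**3. The same deficits in VAS points.** A true deficit of 0.42 points with 50 per group is non-significant:

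- essentially never at the stated SD of 0.21 (deficit 2 SD);
- 11% of the time at SD 0.65;
- 45% at an assumed SD of 1.0;
- 72% at an assumed SD of 1.5.

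**4. What a non-inferiority test could do at this size.** With true difference 0, one-sided 2.5% and 90% power, the smallest margin is (1.960 + 1.282) x sqrt(2/50) = 3.242 x 0.2 = 0.648 SD.

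**5. Like-for-like comparison.** With 50 per group and the margin at 0.648 SD:

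| True deficit (SD) | t test non-significant | Non-inferiority declared |
|---|---|---|
| 0.3 | 68% | 41% |
| 0.4 | 49% | 23% |
| 0.5 | 30% | 11% |
| 0.648 | 11% | 2.5% |

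**6. Whether the planned size suffices.** Using n per group = 2 x (3.242 x SD / margin)^2 with assumed values:

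- SD 1.0, margin 1.0: 22
- SD 1.0, margin 0.5: 85
- SD 1.5, margin 1.0: 48
- SD 2.0, margin 0.5: 337

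The article gives no margin, so this cannot be settled from it.

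**The case against.** **The aim is only to compare.** A t test with a 95% confidence interval can estimate and test a difference, so the trial is not without an answerable question. This stands. It does not remove the mismatch, because the hypothesis follows that aim and goes further than a comparison.

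**The details belong in the analysis plan.** A condensed article may leave much to it, but this one states both the sizing basis and the test, and both are for a difference. A margin would also determine the sample size, so adding one later would depart from the basis in section 2.6.

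**The harm is inferred.** A reader might infer that the plan treats P >= .05 as proof of equal efficacy. The article states no such rule. A reader might also infer that no result could support the hypothesis. That is too strong: on a non-inferiority reading, a significant result favouring ACB would support it.

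**The size of the problem depends on the SD.** This stands. At the stated SD of 0.21, a deficit of 0.4 SD is 0.084 points, and a deficit of 0.42 points would practically never be missed. But an SD of 0.21 does not lead to 50 per group, so it cannot be relied on for reassurance.

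**A margin is no perfect safeguard.** It is tempting to set 49% against 2.5%, but these apply at different deficits. A test with a 0.648 SD margin would itself declare non-inferiority 23% of the time at 0.4 SD, by design, because it accepts deficits below the margin. The fair contrast at the margin is 11% against 2.5%.

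**Conclusion.** The point holds as a mismatch within the document: a comparable-efficacy hypothesis, a sample size built on a difference, and a difference test without a margin. Non-significance under this plan cannot soundly support the hypothesis. The planned confidence interval does not settle it either: at 50 per group its half-width is about 0.39 SD (1.960 x 0.2), and with no margin fixed beforehand there is nothing to judge it against.

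The percentages rest on a two-sided 5% test, 50 analysed per group and normally distributed scores with a common SD. Those given for deficits in VAS points depend on assumed SDs, apart from the stated 0.21. The mismatch itself depends on none of these. It bears on the main conclusion and should be resolved before outcomes are unblinded.

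**What to change.** Choose one of two amendments before outcomes are unblinded. Section 2.2 breaks the randomization key only after all enrolled patients have completed, so this can be done without knowledge of the results.

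- **(a) Keep the claim and make it testable.** State non-inferiority of ACB to EA on one VAS endpoint. Give a margin with its clinical justification. Conclude comparable efficacy only if the upper limit of the planned 95% confidence interval for ACB minus EA lies below that margin. Restate the power for that margin with a credible SD.
- **(b) Drop the claim.** If no margin can be agreed, replace the hypothesis with a comparison of the two techniques, report the difference with its 95% confidence interval, and state that a non-significant result will not be taken as equal efficacy.

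Option (a) costs agreement on a margin and possibly a less favourable stated power. With 50 per group and a true difference of 0, 90% power is reached only for margins of about 0.65 SD or wider; a tighter margin means lower power or more patients. The margin should come from clinical reasoning and not be worked back from the available number. Option (b) costs only wording, but leaves the trial with a weaker claim.

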## Material and method

2

### Study design and patient enrolment

2.1

Approval for the study was granted by the Changji Branch of the First Affiliated Hospital of Xinjiang Medical University (CJ97440). Written informed consent will be obtained from all of the participants. Prospective assessment will be done for 100 patients who are scheduled for unilateral primary TKA surgery in our academic hospital by a single senior surgeon between August 2020 and December 2021. Our study was registered in Research Registry (researchregistry5775) prior to the enrollment start. All surgeons, recovery room and floor nurses, research assistants, statisticians, and patients were blinded to group allocation. Only the anesthesiologists performing the blocks and operating room nurses were not blinded.

Inclusion criteria included the following: planned unilateral TKA; spinal anesthesia; American Society of Anesthesiologists physical status classification score of I to III. Exclusion criteria included the following: unwillingness to participate in the study; general anesthesia; contraindications for the application of ACB such as localized infection and neurological disease in the lower extremity; history of epilepsy; arrhythmia; alcohol or drug dependency; known allergy to local anesthetics; insufficient co-operation for the completion of the visual analog scale (VAS) for pain scores; patients who had an inability to communicate verbally or who were unwilling to give informed consent; American Society of Anesthesiologists physical status classification score of IV.

### Randomization

2.2

Patients were randomized to ACB treatment or EA treatment by a computer random number generator. Every participant received a consecutive study number from 1 to 100 and received the treatment assigned according to the randomization list. The randomization key was first broken when all enrolled patients had completed the study (Fig. 1).

**Figure 1 F1:**
[figure not shown]
Consolidated standards of reporting trials statement flow diagram.

### Intraoperative interventions

2.3

Spinal anesthesia was induced with 3.0 mL 0.5% hyperbaric bupivacaine at the L3/4 interspaces (alternatively at the L2/3 or L4/5 interspaces). Sedation using propofol and intravenous fluid therapy during surgery was administered at the discretion of the anesthetist.

An epidural catheter was placed laterally at the L3/4 or L4/5 level using a 17-gauge Tuohy needle and inserted upward by 5 cm. A test dose of 1% lidocaine (50 mg) was initially injected, and the sensory block was tested after 10 min by applying ice to the ipsilateral thigh. Then, continuous epidural infusion for management of postoperative pain using the catheter that was inserted preoperatively for use during the TKA operation. 20 mL of 0.3% ropivacaine were administered and 0.2% ropivacaine was infused at 5 mL/h for 36 h.

Under ultrasound guidance as above, a 10-cm, 18-gauge Tuohy needle was introduced into the adductor canal. Following dilation of the adductor canal with normal saline, a 21-gauge nerve catheter was threaded up to 3 to 5 cm beyond the needle tip. The guidewire was removed upon the catheter exiting the needle tip while threading to avoid inadvertent advancement of the catheter out of the space. The catheter was then manipulated and normal saline injected to confirm the catheter tip location within the adductor canal on ultrasound visualization, with peri-arterial spread as the endpoint. Up to 5 to 10 mL of normal saline was used in total per catheter placement. 20 mL of 0.3% ropivacaine was then injected via the catheter, following which a continuous infusion of 0.2% ropivacaine commenced at 5 mL/h for 36 h and then removed.

### Surgical procedure and perioperative management

2.4

All of the operations were performed by a single senior surgeon, using a tourniquet and a medial parapatellar approach. Cruciate-retaining implants were used in all cases, as none of the patients were inflammatory arthritis or required posterior cruciate ligament resection and the patella was not changed in any patient. Intra-articular analgesic infiltration was not applied to any patient. For deep vein thrombosis prophylaxis, 40 mg enoxaparin sodium was applied subcutaneously once a day for 4 weeks after discharge.

Preoperative prophylactic intravenous 1 g cefazolin were administered to all patients and postoperative antibiotics were continued for 24 h. In patients with a known allergy to penicillin, 500 mg vancomycin was preferred for prophylaxis. If serum creatinine levels were normal, a dose of 75 mg diclofenac sodium in 100 cc saline was given 8 hourly, for patient controlled analgesia. Otherwise infusion of 1000 mg paracetamol was administered. In both groups, 50 mg tramadol was given as rescue analgesia at the request of the patient inpresenceof intolerable pain despitethe use of standard analgesic regimen.

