### Outcomes and measures

2.5

The primary outcome was VAS pain scores in the immediate postoperative period (postoperative day 0 through 3). VAS scores were recorded by nursing staff, blinded to treatment group, every 6 h throughout the hospital stay. VAS scores on each postoperative day were averaged, and the daily averages were used for analysis. Secondary outcomes included postoperative opioid use, length of hospital stay, activity level during physical therapy, and knee range of motion. Total opioid consumption was calculated by converting opioids consumed to morphine equivalents. Length of hospital stay was calculated by measuring the time from the completion of surgery through discharge for each patient. Activity level during physical therapy was recorded by measuring the steps taken in daily physical therapy sessions. Knee range of motion was measured by the surgeon using a goniometer in the office at 3 weeks postoperatively.

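### The primary VAS is pain after on-request rescue, so unequal rescue shrinks the difference between arms in favour of the trial's similarity hypothesis, and opioid use does not bear on that conclusion

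*Protocol article*

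**What the plan says.** All references are to the protocol article.

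- **Rescue (2.4).** "In both groups, 50 mg tramadol was given as rescue analgesia at the request of the patient". The trigger is pain the patient finds intolerable despite the standard regimen. No timing relative to the VAS readings is given.
- **Primary outcome (2.5).** "The primary outcome was VAS pain scores in the immediate postoperative period (postoperative day 0 through 3"). Readings are taken "every 6 h throughout the hospital stay", and "VAS scores on each postoperative day were averaged, and the daily averages were used for analysis".
- **Place of opioid use (2.5).** "Secondary outcomes included postoperative opioid use, length of hospital stay, activity level during physical therapy, and knee range of motion". Opioid consumption is totalled in morphine equivalents.
- **Hypothesis (Introduction, repeated in the Abstract and Discussion).** "We hypothesized that standard ACB would be as effective as EA for postoperative pain management following TKA". No margin is stated.
- **Test (2.7).** An independent two-sample t test for continuous variables, at P < .05.
- **Background analgesia (2.4).** With normal creatinine, "75 mg diclofenac sodium in 100 cc saline was given 8 hourly, for patient controlled analgesia"; otherwise paracetamol.

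**The concern.** Rescue is triggered by pain, which is also what the primary outcome measures. If one block is weaker, its patients ask for tramadol more often, and some of the readings that enter the daily mean are taken after the drug has acted. The VAS difference is then smaller than the difference the two techniques would show by themselves.

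In a trial that aims to show a difference, this bias is conservative. Here the hypothesis is similarity, so the bias favours the conclusion the investigators expect. With an ordinary t test and no margin, similar VAS scores could be reported as equal efficacy although one arm used more tramadol. That tramadol use would be reported, but as a separate secondary result that the conclusion does not have to take into account.

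The diclofenac sentence raises a related question. An 8-hourly schedule and patient control are different arrangements. If intake is patient-controlled, it too could differ between arms, and the opioid total would not show it.

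**Working it through.** **No stated figure to reproduce.** The article quantifies neither rescue use nor its effect on VAS, so every input in steps 1 to 3 is an assumption. The purpose is to show the direction and a plausible range.

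**1. Assumed model.** VAS on a 0–10 scale. Mean pain without rescue is 4 in one arm and 5 in the other, a true difference of 1.0. The between-patient SD is 1.5 and the within-patient SD 1.0, so a single reading has SD √(1.5² + 1.0²) = √3.25 = 1.803. There are four readings a day. A patient whose pain exceeds a threshold c takes rescue, and that reading is lowered by g points.

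**2. Formula.** With p4 and p5 the proportions of readings above c in the two arms:

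observed difference = 1.0 − g × (p5 − p4), where p_m = P(Z > (c − m)/1.803).

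For c = 5: p5 = P(Z > 0) = 0.500 and p4 = P(Z > 0.555) = 0.289, so the gap is 0.2105. With g = 2 the observed difference is 1.0 − 2 × 0.2105 = 0.58.

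| Rescue above | p4 | p5 | p5 − p4 | Doses per day (4p4 vs 4p5) | Observed, g = 1 | g = 2 | g = 3 |
|---|---|---|---|---|---|---|---|
| 5 | 0.289 | 0.500 | 0.2105 | 1.2 vs 2.0 | 0.79 | 0.58 | 0.37 |
| 6 | 0.134 | 0.289 | 0.1559 | 0.5 vs 1.2 | 0.84 | 0.69 | 0.53 |
| 7 | 0.048 from mean 4, see below | 0.134 | 0.0856 | 0.2 vs 0.5 | 0.91 | 0.83 | 0.74 |
| 8 | 0.013 | 0.048 | 0.0348 | 0.05 vs 0.2 | 0.97 | 0.93 | 0.90 |

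(For c = 7, p4 = P(Z > 1.664) = 0.048.) The loss is 16% to 63% at thresholds 5 and 6, 9% to 26% at 7, and 3% to 10% at 8.

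**3. A milder model.** Suppose rescue lowers only the next 6-hourly reading, and later requests depend on pain as already relieved. A simulation of 400,000 patients per arm with the same means and SDs gives observed differences of 0.67 to 0.90 at thresholds 5 and 6, and 0.85 to 0.98 at thresholds 7 and 8. The direction is unchanged and the size smaller.

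**4. On the scale of the design difference.** Section 2.6 uses a VAS difference of 0.42. Let the weaker arm have an extra share r of rescued patients, and let rescue lower a rescued patient's daily mean by d. Then observed difference = 0.42 − r × d. With r = 0.20 and d = 1.0 it is 0.42 − 0.20 = 0.22; with r = 0.10 and d = 0.5 it is 0.42 − 0.05 = 0.37. Both r and d are assumed.

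**5. Does any stated rule bring rescue into the conclusion?** Sections 2.5 and 2.7 set the primary measure, its daily average, the place of opioid use and the test. None of them makes opioid use a condition for concluding similar efficacy.

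**The case against.** **The article is condensed.** The handling of readings after rescue may be set out in a full protocol or analysis plan that is not shown. That is fair, and the absence of such detail is not the point. The point follows from what the article does fix: the primary measure and its averaging, the rank of opioid use, the test and the similarity hypothesis.

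**Rescue is not ignored.** The aim names the need for additional opioids, the hypothesis speaks of pain management and not of equal VAS, and opioid use is listed first among the secondary outcomes. In the scenarios with the largest attenuation, rescue differs by about 0.6 to 0.8 doses per patient per day, which the opioid outcome could well reveal. This stands. What remains is that such an imbalance need not change the conclusion.

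**VAS regardless of rescue is a legitimate measure.** It is, provided it is read together with rescue use.

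**A stronger reading.** A reader might infer that the weaker block is topped up until pain is equal. The article does not support that. Rescue is a 50 mg dose requested for intolerable pain, not titration to a target score. Intolerable pain may also correspond to the higher thresholds in the table, where the loss is smallest. A reader might likewise infer that diclofenac intake differs by arm; the sentence is only unclear, and the mention of a standard regimen also fits scheduled dosing.

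**Conclusion.** The point holds as one of attenuation and interpretation. The primary VAS measures pain after rescue, unequal rescue moves the arms together, and this favours the stated hypothesis, while the measured opioid use has no bearing on the conclusion drawn.

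The direction requires only that the arm with more pain takes more rescue and that rescue works. The size is unknown. Under the simple model, a true 1.0-point difference appears as about 0.4 to 0.8 if rescue starts above VAS 5 or 6, and as about 0.7 to 0.97 if it starts above 7 or 8. The means, SDs, thresholds and drug effects are all assumed. The documents do not show that the arms would look equal, or that rescue use will differ at all. The diclofenac wording is a smaller, separate inconsistency.

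**What to change.** 1. In 2.5, state that ACB will be called as effective as EA only if two confidence intervals each exclude a prespecified worse-than margin: one for the ACB − EA difference in VAS, the other for the difference in morphine-equivalent opioid use, both over days 0 to 3. State also that the conclusion will not be drawn from non-significant t tests. Without margins, a requirement of being not worse would reduce under 2.7 to two non-significant results.
2. Have nursing staff record a VAS just before each rescue dose. As a sensitivity analysis, use it in place of the next scheduled reading. It has to be collected at the bedside, since it cannot be reconstructed later.
3. In 2.4, reconcile the description of diclofenac as both 8-hourly and patient-controlled, and report diclofenac and paracetamol intake by arm beside the opioid total.

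**Cost.** The claim must be met on two measures, which is harder than on one, and two margins have to be justified. Nurses take one extra reading per rescue dose. The article says that opioids are totalled but does not say that non-opioid intake is captured, so that may need added recording. No change to any drug, dose or rescue rule is implied.
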